### 2.2. Eligibility Criteria

Patients aged at least 18 years old and admitted in a post-stroke rehabilitation unit in the sub-acute phase (15 days to 6 months after the onset of stroke symptoms) will be eligible for the study. Patients with left USN subsequent to a first unilateral right hemispheric stroke will be included. The diagnosis of stroke will have to be confirmed by computed tomography or magnetic resonance imaging. Screening for USN will be performed by the c-BIT [16], a score ≤ 129 defining USN. Patients unable to give informed consent, pregnant women, patients with skin lesions on the areas for electrode placement or having history of metal-in-cranium injury, epilepsy, vestibulo-cochlear illness or cardiac pacemaker will not be included.

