The Wheelchair navigation test [21], illustrated in Figure 3, aims at investigating spatial navigation skills and extra-personal neglect. The ride will be carried out once in each direction (A-B and B-A) to balance the number of obstacles and turns to the left and right. The time taken to finish the course will be measured and the number of bumps counted. Navigation quality will also be observed qualitatively (obstacle avoidance, goal strategy, perseverations).

Each test will be carried out several times over the study by a trained occupational therapist:

Baseline assessment (Pre): During the first week, each test (except for the CBS realized only once) will be repeated three times in order to obtain a reliable estimation of the participants’ performance level (mean values) before starting the experimental interventions.

Follow-up assessments: These will take place just at the end of the first experimental session (Postsession1), after the first and third weeks of the protocol (Postweek1 and Postweek3, respectively) and there will be a final evaluation three weeks after its ending (Postweek6). In addition, all patients will be asked about their expectations and satisfaction regarding the treatment at the end of each week of intervention.

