### 2.6. Statistical Analysis

CBS scores, those of personal neglect, mean egocentric errors and mental evocation, the time needed to finish the wheelchair course and the number of bumps in each direction will be entered as quantitative data.

After having verified the required assumptions about data distributions (Shapiro–Wilk test of normality, Levene’s test of homoscedasticity, Box’s M-test of covariance homogeneity and Mauchly’s test of sphericity), a mixed analysis of variance (with repeated measures for the SSA) will be performed on each quantitative variable with test periods (Pre, Postsession1, Postweek1, Postweek3, Postweek6) as within-subject factors and treatment groups (control, left-NMV, left-NMV + sham-tDCS, left-NMV + a-tDCS) as between-subject factors. Post hoc tests will be conducted using Tukey’s honestly significant difference method when needed, and *p*-values will be adjusted with the Bonferroni method. Size effects will be reported using the η2 (Eta-square) for each ANOVA and Cohen’s d for each Tukey’s post hoc test, along with confidence intervals.

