If the conditions for using parametric tests are not met, then non-parametric statistical analyses of comparisons between test periods and groups will be performed. For each treatment group, we will perform a Friedman test to analyze the effect of the test period on each quantitative variable independently. When a Friedman test is significant, post hoc Wilcoxon signed rank tests with the Bonferroni adjustment method will be used to perform pairwise comparisons between each of the five time points. Kruskal–Wallis tests will be performed to compare the treatment groups. First, a Kruskal–Wallis test will be performed on the sum of ranks of the scores in each group before the first session in order to ensure that the initial mean scores (Pre) are equivalent between groups. Second, the effect of treatment will be calculated for each participant at each post-session assessment (Postsession1, Postweek1, Postweek3, Postweek6) by subtracting the mean initial score (Pre) from each quantitative data, independently. In order to analyze the effect of the treatment received on the evolution of quantitative data, Kruskal–Wallis tests will be performed on the sum of ranks of the Post–Pre score differences in each group. When the Kruskal–Wallis test is significant, post hoc pairwise comparisons between groups will be calculated, and the *p*-value will be adjusted by the Steel–Dwass–Critchlow–Fligner method.

Any participant with a missing score on any of the assessment sessions will be excluded from the statistical analysis for that specific test.

All statistical analyses will be performed using R software (version 2021.09.1 Build 372). The threshold for statistical significance will be set at α = 0.05.

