
There are some inherent features of our study protocol that deserve cautious consideration. Particular attention will be directed to the phenomena of limb activation and motor extinction [36,37], since our protocol is designed around the performance of voluntary upper limb movements simultaneously to stimulation sessions in USN patients. Although it has been shown in the literature that the use of the contralesional arm in the neglected hemi-space significantly reduces the severity of USN [37], these patients generally have great difficulty in mobilizing it in the early post-stroke stages. Moreover, the simultaneous use of both upper limbs in the neglected hemi-space limits or even suppresses the previously observed beneficial effects [36,37] possibly by perceptual “overshadowing” of the contralesional arm movements by the ipsilesional ones, according to Robertson and North [37]. Therefore, the therapists will carefully avoid bimanual activities in the neglected hemi-space, but exercises will be allowed with the right upper limb instead of the left one if the latter is too impaired to effectively perform them in initial phases of rehabilitation. This gradual increase in task complexity is also intended to maintain high motivation levels. Other vigilance points will be taken into account. We will be watchful of population homogeneity, hence the need to include a sufficient number of patients. We will compare the evolution of each patient from baseline according to his affiliation group, given the possibility of inter-subject variability in responsiveness. In addition, the long-term effects of tDCS should be clarified, and its optimal targets for motor and spatial rehabilitation have not been sufficiently studied yet. There is also a risk of misuse or overuse of non-invasive stimulations. Finally, local rehabilitation teams will be coordinated for inter-site standardization of inclusion, occupational therapy tasks, test performance and stimulation tools use.

In conclusion, the originality of our study lies in this novel combination of non-invasive stimulation techniques with low attentional demands and their application during occupational therapy sessions, thus ideally complementing conventional rehabilitation. The results of our multimodal approach should also provide interesting data to reconsider hemi-spatial theories suggesting a dominant function of the right hemisphere or others supporting an “interhemispheric competition” model [49].

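### A wheelchair ride that is not finished has no time, so the stated exclusion rule would discard the worst result on this secondary outcome as if it were missing

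*Protocol article*

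**What the plan says.** Section 2.4.3 defines the wheelchair outcome: "The time taken to finish the course will be measured and the number of bumps counted". Section 2.6 takes this into the analysis: "the time needed to finish the wheelchair course and the number of bumps in each direction will be entered as quantitative data". It also fixes the rule for incomplete data: "Any participant with a missing score on any of the assessment sessions will be excluded from the statistical analysis for that specific test". Five assessments count, since the model uses "test periods (Pre, Postsession1, Postweek1, Postweek3, Postweek6) as within-subject factors". At baseline "each test (except for the CBS realized only once) will be repeated three times", and the mean is used. Each assessment has one ride in each direction.

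Entry is limited on neglect severity from one side only: "Screening for USN will be performed by the c-BIT [16], a score ≤ 129 defining USN" (section 2.2). No lower limit is given, and being able to complete a wheelchair course is not a stated condition. The article gives no value for an unfinished ride.

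**The concern.** A score defined as the time to finish exists only for those who finish. A patient who cannot finish, or whose ride is stopped, has performed as badly as the test allows, yet has no number to enter. The exclusion rule then removes that patient's wheelchair data at every assessment.

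Two things are at stake. First, groups of 12 become smaller. Second, finishing at a later visit may depend on the treatment received, so the exclusion selects patients after randomisation and the arms can lose different numbers. A patient unable to finish at Pre who finishes at Postweek3 shows the largest change that the test could record, and contributes nothing. This is the one test that the article assigns to navigation and extra-personal neglect.

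**Working it through.** **The plan's own figure.** Section 2.5 gives 48 patients in four groups: 48 / 4 = 12 per group. It states that no power calculation was possible, so there is no effect size, SD or power to reproduce.

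**The rules side by side.** (1) The score is the time to finish (2.4.3, 2.6). (2) No finish therefore means no time. (3) One missing score at any of five assessments removes the patient from that test (2.6). (4) Nothing in the entry criteria (2.2) rules out patients who cannot finish. Steps 1 and 3 are stated. Step 2 follows from the definition unless some other document gives an unfinished ride a value.

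**Size, on assumed rates.** The documents give no rate of non-finishing, so these figures are illustrations only.

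*Non-finishing independent between assessments,* with probability q at each: share excluded = 1 − (1 − q)^5.
- q = 2%: 1 − 0.98^5 = 9.6%, or 4.6 of 48
- q = 5%: 1 − 0.95^5 = 22.6%, or 10.9 of 48
- q = 10%: 1 − 0.90^5 = 41.0%, or 19.7 of 48

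*Non-finishing driven by severity* (simulation, 400,000 patients per arm). Assumptions: latent time score with SD 1; correlation 0.8 between assessments; common recovery of 0.5 SD and true treatment effect of 0.50 SD at Postweek3; a ride is unfinished when the latent score exceeds a cutoff that gives the stated rate at Pre; one Pre value per patient; anyone with an unfinished ride at any of the five assessments is excluded. The effect is either the same for all patients or multiplied by 1 + 0.4 × severity (not below zero).

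| Unable at Pre | Effect | Excluded: control / treated | Left of 12: control / treated | Estimated effect (true 0.50) |
|---|---|---|---|---|
| 5% | uniform | 8.3% / 7.3% | 11.0 / 11.1 | 0.50 |
| 10% | uniform | 16.0% / 14.2% | 10.1 / 10.3 | 0.49 |
| 20% | uniform | 29.9% / 26.9% | 8.4 / 8.8 | 0.49 |
| 30% | uniform | 42.0% / 38.6% | 7.0 / 7.4 | 0.48 |
| 5% | larger if severe | 8.5% / 7.0% | 11.0 / 11.2 | 0.47 |
| 10% | larger if severe | 16.1% / 13.7% | 10.1 / 10.4 | 0.44 |
| 20% | larger if severe | 29.9% / 26.4% | 8.4 / 8.8 | 0.41 |
| 30% | larger if severe | 42.1% / 38.5% | 6.9 / 7.4 | 0.37 |

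In the 20% uniform case, 17.0% of treated and 12.8% of control patients go from unable at Pre to able at Postweek3. All of them are excluded, so that contrast between arms is never seen.

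**What lost patients cost.** In a normal approximation the smallest detectable difference grows as √(12/n), whatever the significance level. For 10 per group this is √(12/10) = 1.10, and for 8 per group √(12/8) = 1.22, so 10% and 22% larger than with 12.

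**The case against.** The strongest objection is that the key link is inferred. The article does not say that an unfinished ride is scored as missing, that rides may be stopped, or that any patient will fail to finish. The test comes from an earlier publication, and the scoring of an unfinished ride could be set out there or in a full protocol. This stands as a limit: the problem arises only if some patients do not finish and no other document gives them a value. It does not remove the point, because the article itself states both the definition by finishing and the exclusion rule, and together they give the poor result.

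Three further objections stand in part.
- Three repeats at Pre may leave a baseline mean even if one ride fails. The article does not say, and the simulation ignores it.
- The harm runs through the general exclusion rule. However, replacing that rule with a model that uses the patient's other visits would still assume that absent times are missing at random, whereas these are absent because the performance was poor.
- The outcome is secondary, and navigation quality is also observed qualitatively, so an unfinished ride is not wholly unrecorded.

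A reader might also infer more than the text supports. The Discussion's remark on early motor difficulty concerns use of the contralesional arm in therapy exercises. It says nothing about driving a wheelchair and is not evidence of non-finishing. Nor can a power loss be stated for this trial: the article gives no effect size or non-finishing rate, and it plans a mixed ANOVA or a four-group rank test with adjusted comparisons, so power figures from an unadjusted comparison of two groups would not be its own.

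**Conclusion.** The point holds as a conditional flaw in a secondary outcome. If any patient cannot finish, the plan as written discards the worst result and may discard the largest improvement.

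The main cost is lost patients: on the assumed baseline rates of 5% to 20%, about 1 to 4 of 12 controls. The arms also lose slightly different numbers. A reader might infer that the treatment effect is necessarily biased toward zero. The documents do not support that. With the same effect at every severity the bias is small (0.48 to 0.50 against 0.50). Material bias appears mainly if severe patients gain most, which is an assumption. The primary outcome, the Catherine Bergego Scale, is not affected by this scoring problem.

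**What to change.** Before the first patient:
- Set one maximum ride time. Record an unfinished or stopped ride at that maximum as an observed score, also within the Pre mean, and exempt it from the exclusion in section 2.6.
- Use the rank-based analysis already described in section 2.6 for this outcome. That analysis ranks Post–Pre differences, and a patient at the maximum on both visits has a change of zero, which ranks above a finisher who slowed slightly. So add a rank comparison of the Post score itself as a sensitivity analysis.
- Report the number of non-finishers by arm and visit.
- Report bump counts together with completion status. A partial ride offers fewer obstacles to hit, and a worst rank for bumps could not be used in an analysis of differences.
- Keep the term missing for rides not attempted for reasons unrelated to ability.

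The cost is a few sentences in the outcome definition and analysis section, with no extra visit or procedure. The maximum is somewhat arbitrary, and mean times become harder to read where patients are capped.

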#### 2.4.4. Monitoring and Blinding

The trial sponsor will assign a supervisor to monitor 10% of the experimental occupational therapy sessions to ensure that they are conducted in accordance with the protocol. In addition, 10% of the evaluations will be monitored. The researcher who will generate the patients’ allocation sequence will not perform the neuropsychological evaluation, nor apply therapeutic stimulations. The therapist who will perform USN evaluations before and after the treatment will be blind to the patients’ group assignment.

### 2.5. Sample Size Calculation

To determine the number of left USN patients to include, we sought to perform an a priori headcount calculation based on published work in the field. However, none of them have combined NMV and tDCS or used the CBS score as the primary endpoint. No a priori power calculation could therefore be performed, but we were inspired by the number of patients included in the works of Làdavas et al. [32] and Turgut et al. [33], both of whom used tDCS on USN patients, the former combined with visual prisms and the latter with optokinetic drift. These two studies included 30 and 32 patients, respectively, which were divided for the first in two groups of 11 patients and one group of 8, and for the second in two groups of 16 patients. Thus, we estimated that 48 patients would be necessary for our study, randomly and homogeneously distributed in each of the 4 groups. To ensure that the target number of patients is recruited, three neurological rehabilitation centers admitting each year a large number of patients meeting the inclusion criteria will be involved. We will verify a posteriori that the groups do not differ in sex, mean age, education, duration of illness, or baseline CBS scores, and that they have similar stroke locations.

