## 2. Materials and Methods

This multicentric prospective randomized controlled superiority trial will focus on assessing the benefits of our therapeutic protocol on independence in daily life activities, neuropsychological aspects of different spatial components of USN (personal, extra-personal and representational neglect) and egocentric spatial perception assessments, using a mixed measurement design. The HEMISTIM protocol will take place in three neurological rehabilitation centers in Grand-Est and Provence-Alpes Côte d’Azur regions, France.

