#### 2.4.1. Inclusion in Groups

The first week will allow us to include patients with left USN and to randomly assign them to four independent parallel groups (centralized randomization in a 1:1 ratio performed using a custom made algorithm on Matlab (MathWorks, Inc., Natick, MA, USA) by a blinded investigator: a control group receiving no additional treatment to conventional occupational therapy sessions and three experimental groups receiving in addition to the usual treatment either left-NMV, left-NMV + sham-tDCS or left-NMV + a-tDCS experimental treatments, administered by trained occupational therapists.

In these three experimental groups, each patient will be equipped with vibratory stimulators during conventional occupational therapy sessions taking place on Monday, Wednesday and Friday for three weeks from the second week on. The left-side NMV vibrator will be activated during the first 15 min of the occupational therapy session (lasting 45 min), as previously described [21,35]. In the two experimental groups receiving sham or a-tDCS, electrodes will be placed as described above. A continuous 2 mA current will be delivered for 20 min in the left-NMV + a-tDCS group, 5 min before (patients will be seated in a quiet room) and during the first 15 min of the occupational therapy session, simultaneously to the NMV stimulation. The current will be automatically turned off after 20 s in the left-NMV + sham-tDCS group, allowing the reproduction of the initial mild itching sensation at the beginning of active tDCS, thus ensuring that the patient stays blind to the activation status of the device. In the case of adverse events or unintended effects of trial interventions, the investigator who enrolled the patient will report its occurrence to the trial sponsor through a report form provided in the case report form.

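### A non-significant baseline test cannot show the arms are equivalent, and using Pre as an outcome period or subtracting it, instead of adjusting for it, loses precision

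*Protocol article*

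**What the plan says.** **Sample size and allocation.** Section 2.5 sets the size by analogy with two earlier studies: "Thus, we estimated that 48 patients would be necessary for our study, randomly and homogeneously distributed in each of the 4 groups". On power it says: "No a priori power calculation could therefore be performed". Section 2.4.1 describes "centralized randomization in a 1:1 ratio".

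**Baseline checks.** There are two.
- Section 2.5: "We will verify a posteriori that the groups do not differ in sex, mean age, education, duration of illness, or baseline CBS scores". No test, margin or consequence is given.
- Section 2.6, only if the parametric assumptions fail: a Kruskal-Wallis test on the Pre scores "in order to ensure that the initial mean scores (Pre) are equivalent between groups". This one is a significance test, and it is read as showing equivalence.

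**Use of baseline in the analysis.** Section 2.6 gives two paths.
- Parametric: a mixed ANOVA with group as the between-subject factor and five test periods as the within-subject factor. Pre is the first of the five.
- Non-parametric: each participant's treatment effect is formed "by subtracting the mean initial score (Pre) from each quantitative data, independently", and the differences are compared between groups by Kruskal-Wallis tests.

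No covariate appears in either path. Section 2.4.3 adds that the CBS, the primary outcome, is measured once at baseline, while the other tests are averaged over three sessions.

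**The concern.** There are two linked problems.

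First, failing to reject a null hypothesis of no difference does not establish equivalence, least of all with 12 per arm. After proper randomisation, any baseline difference is due to chance, so the test asks a question whose answer is already known. A reader told that the groups were shown to be equivalent would be misled. The result also feeds into nothing: the analysis is the same whether or not the test is significant.

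Second, the useful step, which is to adjust for the recorded baseline, is missing from both paths. In the mixed ANOVA, the group-by-period contrasts against Pre are differences in mean change, so they are change-score comparisons. The group main effect averages over all five periods, including the one before any treatment, and so is diluted. The fallback uses change scores outright. A change score fixes the slope of follow-up on baseline at 1. When the true slope is below 1, this over-corrects: an arm that starts worse by chance appears to gain more. It also adds baseline noise to the estimate. In a trial of 48 with no power calculation, the lost precision matters.

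**Working it through.** **Inputs from the article.** 48 patients in 4 groups, so 48/4 = 12 per arm; alpha 0.05 (Section 2.6), taken as two-sided. This division is the only plan figure that can be reproduced, because no effect size, SD or power is stated.

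**Assumptions.** Scores are standardised to SD 1, with the same SD before and after treatment. The pre-post correlation rho is varied from 0.4 to 0.9.

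**1. What a null baseline test can show.** The 95% confidence interval for the baseline difference between two arms, with pooled error on 44 df, has half-width

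t(0.975, 44) × √(2/12) = 2.015 × 0.408 = 0.82 SD.

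A difference near zero is thus compatible with a gap of about 0.8 SD either way. Under correct randomisation, the expected gap between the highest and lowest of four arm means is 0.59 SD (simulation), and it reaches 0.5 SD in 61% of trials. For two given arms, the expected absolute gap is √(2/12) × √(2/π) = 0.408 × 0.798 = 0.33 SD.

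**2. What remains of an imbalance.** With a chance imbalance d, the change-score estimate shifts by −(1 − rho) × d. For d = 0.5 SD:

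| rho | shift (SD) |
|---|---|
| 0.5 | −0.25 |
| 0.7 | −0.15 |
| 0.8 | −0.10 |
| 0.9 | −0.05 |

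In simulated four-arm trials, the regression of the change-score estimate on the imbalance had a slope of about −0.60 at rho 0.4, −0.40 at 0.6 and −0.20 at 0.8. For ANCOVA it was about 0 throughout.

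**3. Precision.** Up to a common factor, the variance of a pairwise contrast is 2(1 − rho) for change scores and 1 − rho² for ANCOVA. Estimating one slope multiplies the ANCOVA variance by 1 + 1/(48 − 4 − 2) = 1 + 1/42 = 1.024.

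| rho | change | ANCOVA × 1.024 | reduction |
|---|---|---|---|
| 0.5 | 1.00 | 0.75 × 1.024 = 0.768 | 23% |
| 0.7 | 0.60 | 0.51 × 1.024 = 0.522 | 13% |
| 0.8 | 0.40 | 0.36 × 1.024 = 0.369 | 8% |
| 0.9 | 0.20 | 0.19 × 1.024 = 0.195 | 3% |

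Simulation agrees to within about one percentage point. At rho 0.5, change scores would need 48 × 1.00/0.768 = about 63 patients to match ANCOVA with 48; at rho 0.8, 48 × 0.40/0.369 = about 52.

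**4. Power and type I error.** For an illustrative pairwise effect of 1.0 SD, 12 against 12, alpha 0.05 without multiplicity adjustment, simulated power was 61% (change) against 75% (ANCOVA) at rho 0.4, 76% against 83% at 0.6, and 97% against 98% at 0.8. With no effect, both methods rejected in about 5% of trials (4.8 to 5.2%).

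**The case against.** The strongest reply is that the planned analysis is valid. Change scores are unbiased over repeated randomisation and hold their error rate, and both paths use Pre in some way. That stands: the issue is efficiency and the conditional effect of imbalance, not validity.

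Several stronger readings are tempting, but the article does not support them.

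- **Two batteries of baseline significance tests.** A reader might count a test for each variable listed in Section 2.5 and compute a false-alarm rate. That sentence names no test. The only stated one is the Kruskal-Wallis test in the fallback.
- **Baseline imbalance passing in full into the result.** Only the fraction (1 − rho) remains. The 0.59 SD figure is the expected spread between the extreme arms, not the distortion of a typical contrast.
- **Time since stroke and centre must be modelled, and allocation blocked by centre.** Patients enter from 15 days to 6 months after stroke, and the trial "will take place in three neurological rehabilitation centers", so both are reasonable candidates. But the article gives no figure for their prognostic strength, and Section 3 plans standardisation between sites. A journal article commonly leaves blocking and stratification to the full protocol. Adding log time and two centre terms to Pre also uses four parameters. If those terms are not prognostic, the variance factor is 1 + 4/(48 − 4 − 4 − 1) = 1 + 4/39 = 1.103. The gain over change scores is then about 17% at rho 0.5, 6% at 0.7 and 1% at 0.8, with a loss of about 5% at 0.9.

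It may also be said that covariates can be left to an analysis plan. That does not answer the point here: Section 2.6 fixes the model, its factors, the fallback and the post hoc tests, and what it fixes makes Pre an outcome period or subtracts it.

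**Conclusion.** The point holds as a recommended improvement, not as a flaw that invalidates the trial. The claim that a Kruskal-Wallis test on Pre ensures equivalence is wrong at any rho. The handling of baseline is inefficient in both paths, and by how much depends on rho, which the article does not give. The gain is worthwhile at moderate correlation (23% lower variance at 0.5), modest at 0.7 to 0.8 (13% to 8%) and negligible near 0.9. The calculation assumes equal SDs before and after treatment and a common linear slope. The single baseline CBS measurement leaves measurement error in Pre that averaging reduces for the other tests. This tends to lower rho and favours adjustment for the primary outcome.

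A reader might infer that the planned results would be biased or the error rate inflated. Neither follows.

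**What to change.** 1. In Section 2.6, delete the Kruskal-Wallis test on Pre scores and its equivalence claim. In Section 2.5, replace the a posteriori verification with a descriptive baseline table by group, without p-values.
2. Analyse the four follow-up scores (Postsession1 to Postweek6) with the participant's own Pre score as covariate, by ANCOVA at each time point or by one baseline-adjusted repeated-measures model. Pre is then no longer an outcome period. This still serves the aim in Section 3 of comparing evolution from baseline, because with Pre as covariate the group contrast is the same whether follow-up or change is the response.
3. Where parametric assumptions fail, use a rank-based ANCOVA on the follow-up score with Pre as covariate, in place of Kruskal-Wallis tests on differences.

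The cost is a change of wording and one degree of freedom for a common slope. No new data are needed, since Pre is already collected. If rho is about 0.9, the gain is small. Time since stroke and centre may be added if they are pre-specified and believed prognostic, but they are not part of the required change.
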